## II. Synopsis

|                                                       |                                                                                                                                                                                                                                       |
|-------------------------------------------------------|---------------------------------------------------------------------------------------------------------------------------------------------------------------------------------------------------------------------------------------|
| Sponsor:                                              | Witten/Herdecke University
[name]
[name]
represented by:
Centre for Clinical Studies at Witten/Herdecke University
[name]
[name]                              |
| Head of the clinical trial:                           | [name]. med. [name]
Viszeral-, Gefäß- und Transplantationschirurgie, Klinikum Köln
Merheim, [name]
[name]
[contact]                                            |
| Title of the clinical trial:                          | BIOLAP: Biological versus synthetic mesh in laparoscopic
hernia repair - a randomised multicentre, prospective, self-
controlled clinical trial                                                                                 |
| Indication:                                           | Bilateral primary inguinal hernias                                                                                                                                                                                                    |
| Type of examination,
study design/
methodology: | Prospective, intrinsically controlled, two-arm comparative
study of two CE-certified medical devices in the intended
indication with regard to efficacy                                                                         |
| Number of patients:                                   | 496 patients with bilateral inguinal hernia → 992 hernias                                                                                                                                                                             |
| Primary study objective:                              | It should be shown that the use of biological mesh material for
laparoscopic hernia treatment results in significantly less
postoperative pain than the use of synthetic mesh material,
without an increased recurrence rate |

Outcome:

Primary Outcome:

- Pain reduction after 6 months measured with a visual analogue scale (VAS 0-10)
- Recurrence rate after 2 years

Secondary Outcome:

- Frequency and intensity of pain at other time points (one week and one year after surgery)
- Recurrence rate after one year
- Local infection of the surgical site
- Mesh dislocation
- Haematoma
- Seroma
- Patient satisfaction (overall result, foreign body sensation, paraesthesia, one week and one year after surgery)

Evaluation criteria:

Effektiviness:

- The expected advantage of the biological mesh is 0.5 points on the 0-10 VAS.
- An assumed recurrence rate after 2 years of 5 % for the synthetic mesh material contrasts with a recurrence rate of  $\leq 8$  % for the biological mesh material.

Security:

- Number and type of complications such as re-interventions or replacement of the mesh

Diagnosis and main  
inclusion criteria:

Diagnosis/main inclusion criterion:

- Patients with bilateral primary inguinal hernias

Further inclusion criteria:

- Patient is suitable for laparoscopic surgery

Main exclusion criteria:

- Recurrent Hernia
- Incarcerated Hernia
- Presence of an acute systemic infection

Test product:

Type of application:

Not two specific products but two types of materials are compared. Each study centre must use commercially available mesh material. However, the following requirements apply:

- CE-certified meshes
- The synthetic mesh materials should be made of polypropylene, polyester or PVDF, have large pores and be lightweight ( $< 100 \text{ g/m}^2$ ).
- The biological mesh material should consist of a perforated, non-crosslinked, acellular and collagenous matrix.
- The meshes should have a minimum size of 10x15 cm
- The meshes can be fixed with adhesive

Comparative therapy,  
dosage and method of  
application:

Both mesh materials are used for each patient and compared directly with each other (self-controlled design). Other procedures/materials are not usual for this indication. The usual laparoscopic implantation in hernia repair is performed according to IEHS guidelines.

Duration of therapy:

The duration of treatment corresponds to the clinical routine and the procedure itself takes about 1 hour. Both hernias are treated in one procedure.

Schedule:

|                                                                      |            |
|----------------------------------------------------------------------|------------|
| Inclusion of the first patient
(first patient first visit, FPFV): | 01.08.2017 |
| Inclusion of last patient (LPFV):                                    | 31.07.2020 |
| End of examination of the last patient (LPLV):                       | 31.07.2022 |
| Integrated final report:                                             | 31.07.2023 |

Statistician:

[name]. [name]  
Institute for Research in Operative Medicine  
Witten/Herdecke University  
[name]  
[name]

**Statistical methods:** Hernias, not patients, are randomised. In each patient, one hernia is treated with a synthetic mesh and the hernia on the other side with biological mesh material.

**Primary endpoint efficacy:**

All endpoints are analysed in the intention-to-treat population. In the absence of follow-up examinations, the LOCF (Last Observation Carried Forward) principle is used. Two primary endpoints are analysed (recurrence and pain); the p-value is adjusted according to Bonferroni. Pain reduction is determined separately for each side. The pain analysis is performed using the Wilcoxon signed-rank test for paired samples (alpha 0.025, two-sided). The evaluation of the recurrence rate requires a minimum observation period of 2 years. The difference in recurrence rates is expressed as a 95 % confidence interval (one-sided).

**Safety:**

Complications are compared with the McNemar test for the event rate in paired data.

**Secondary endpoints:**

Early recurrence rates (up to one year post-op) are analysed descriptively using Kaplan-Meier. Pain intensity and frequency at all recorded time points are analysed with a non-parametric rank test.

**GCP conformity:** This trial will be conducted in accordance with the current version of the protocol, the internationally recognised guideline Good Clinical Practice (ICH-GCP) and Good Clinical Practice for the Investigation of Medical Devices (DIN EN ISO 14155), including the archiving of essential documents, but with an adapted scope due to the study design (CE-certified medical devices in indication § 23b MPG).

Financing:

Funding is provided by the German Research Foundation  
(grant number HE 1586/5-1)

#### IV. List of abbreviations

| Abbreviation | Meaning                                                                                  |
|--------------|------------------------------------------------------------------------------------------|
| ADE          | Adverse Device Effect                                                                    |
| ASADE        | Anticipated Serious Adverse Device Effect                                                |
| CRF          | Case Report Form                                                                         |
| DALY         | Disease-adjusted life years                                                              |
| DSMC         | Data Safety Monitoring Committee                                                         |
| IFOM         | Institute for Research on operative medicine                                             |
| IFU          | Instructions For Use                                                                     |
| LKP          | Leiter der klinischen Prüfung (Principal Coordinating Investigator)                      |
| SADE         | Serious Adverse Device Effect                                                            |
| SUSADE       | Suspected Unexpected Serious Adverse Device Effect                                       |
| TAPP         | transabdominal preperitoneal plasty                                                      |
| TEP          | total extraperitoneal plasty                                                             |
| USADE        | Unanticipated Serious Adverse Device Effect                                              |
| ZKS-UW/H     | Zentrum für klinische Studien der Universität Witten/Herdecke/Center for clinical trials |

## 1. Introcution

Inguinal hernia repair is one of the most common surgical procedures, with more than 20 million being treated each year (6). In the USA alone, approximately 4.5 million people are affected (1). Bilateral inguinal hernias occur in approximately 30% of adult cases (2). The risk of developing an inguinal hernia in the course of a lifetime is 27% for men and 3% for women (3). More than 700 deaths each year in England and Wales are attributable to abdominal hernias, a higher number than for gallstones, pancreatitis or inflammatory bowel disease (4). Abdominal hernias are generally considered to be amenable to surgical repair, so this high mortality rate is generally considered preventable (5). A 2010 study by the Global Burden of Disease project found that 11 DALYs per 100,000 population per year are attributable to inguinal hernias (7).

Inguinal hernias can be treated surgically in various ways: open procedures, open procedures with mesh inserts and laparoscopic procedures with mesh inserts (8). Laparoscopic procedures have proven their worth as they provide very good results and also result in less post-operative pain and wound infections (9). However, hernia recurrence is a clinical problem, with a recurrence rate of 1-10% (10) and the occurrence of chronic pain after hernia repair is also problematic with a frequency of 11-54% (11, 12).

For laparoscopic hernia repair, two standard procedures have been established as equivalent in terms of recurrence rate and occurrence of pain: TAPP (transabdominal preperitoneal plasty) and TEP (total extraperitoneal plasty). Nowadays, it common practice to use synthetic mesh material for the plastic. However, there is increasing evidence that biological mesh material offers advantages in terms of the occurrence of chronic pain due to the different postoperative remodelling without disadvantages of a lifelong artificial implant (13).

To date, however, there have been no studies that have specifically investigated whether the presumed advantage of biological mesh material can also be empirically proven.

## **2. Aims of the clinical trial**

The aim is to show that the use of biological mesh material for the laparoscopic treatment of inguinal hernias causes significantly less pain postoperatively than the use of synthetic mesh material (superiority), without an increased recurrence rate (non-inferiority).

### **2.1. Rationale of the clinical trial**

A literature search in the PubMed database using the search terms biological mesh (biomesh) and inguinal hernia (groin hernia) found only one study comparing biological mesh material in open hernia repair and also reporting only a 1-year follow-up (13). This study showed initial indications of a reduction in pain when using the biological mesh material, while the recurrence rate appeared to depend more on the surgeon's experience. The only study dealing with the use of biological mesh material in the TAPP procedure is a retrospective case series of 11 patients, which confirms that the biological material is very suitable for laparoscopic hernia repair. However, there is no self-controlled, prospective, multicentre study as envisaged in the present case. The result of the literature search was also confirmed in a recently published review article (15).

Since, despite many indications of the advantages of using biological mesh material for hernia repair and its frequent use in everyday clinical practice, there is no reliable evidence in favour of using biological rather than synthetic mesh material, we believe that a prospective study is necessary. If it can be proven that biological mesh material for hernia repair has no disadvantage in terms of recurrence rate and pain intensity/frequency, this could be a milestone in hernia repair and make biological mesh material the standard implant for laparoscopic repair of inguinal hernias.

The central element of the study design is self-control. Only patients with bilateral hernias are included and a biological mesh is then implanted on one side of each patient and the synthetic mesh material is used on the other side. Which side is treated with which material is decided in advance by randomisation. Each patient is therefore their own control and allows an ideal comparison of the two materials without additional confounding variables.

Due to the limited data on the use of biomeshes in hernia surgery, the study is to be extended to up to ten years of follow-up after completion of the two-year observation phase. Participation in the long-term data collection is voluntary for the study participants, all study participants can separately consent to further participation in the study. During the further follow-up, each patient will remain in the study until bilateral recurrence, up to a maximum of ten years after surgery.

The study endpoints remain the same. Long-term observation makes sense, as no studies with a sufficiently high number of cases are known to date that observe the use of biomeshes over a longer period of time. In addition, many recurrences only occur after more than two years [17].

## **2.2. Primary Outcome**

This study has two primary endpoints: Pain intensity after 6 months, measured with the visual analogue scale VAS (0-10) and the recurrence rate after 2 years.

Pain intensity is tested for difference, while non-inferiority is tested for recurrence rate.

## **2.3. Secondary outcome**

- Intensity of pain at other time points (see table Flow Chart)
- Recurrence rates within one year after surgery
- Complications e.g. infections, mesh dislocations
- Haematoma
- Seroma
- Patient satisfaction (overall result, foreign body sensation, paraesthesia) at various points in time (see table flow chart)

#### 3.4. Data Safety Monitoring Committee (DSMC)

Complications are documented in the CRF. Those related to the surgical procedure are periodically reviewed by the LKP and the DSMC to determine whether they are (serious) adverse device events (ADEs or SADEs). Members of the DSMC will be:

- [name] (Ordination [name], Zell am See, Austria)
- [name] (Institute for Quality and Efficiency in Health Care, Köln, Germany)

### 3.5. Test laboratories and other technical facilities

The laboratory tests planned as part of this clinical trial are carried out in the clinical laboratories of the participating trial centres.

### **3.7. Investigator and study sites**

The clinical trial will be conducted in a multi-centre setting at 22 trial sites in Germany. If necessary, further qualified trial sites can be included in the clinical trial.

A list of the trial sites with the names of the principal investigators can be found in Annex 10.1. The information on trial sites, principal investigators and other investigators as well as the other trial personnel will be continuously updated in a separate list. The final list will be attached to the final report of the clinical trial.

#### Requirements for Investigators and study sites

Investigators, monitors and study management must be GCP trained, or will be by the time they are required to fulfil their responsibilities. The trial centres and investigators must have proven expertise in the field of laparoscopic hernia surgery and be able to perform the operation in accordance with the Guidelines for laparoscopic (TAPP) and endoscopic (TEP) treatment of inguinal hernia of the International Endohernia Society (IEHS).

### **3.8. Financing**

Funding is provided by the German Research Foundation (DFG) under the grand number HE 1586/5-1.

## 4. Study realisation

### 4.1. General study design

Prospective, intrinsically controlled, two-arm comparative study of CE-certified medical devices in the intended indication with regard to efficacy.

#### 4.1.1. Timetable

**Table 1: Schedule of the trial**

|                                                                   |            |
|-------------------------------------------------------------------|------------|
| Inclusion of the first patient (first patient first visit, FPFV): | 01.08.2017 |
| Inclusion of last patient (LPFV):                                 | 31.07.2020 |
| End of examination of the last patient (LPLV):                    | 31.07.2022 |
| Integrated final report:                                          | 31.07.2023 |

Potential study participants are patients with bilateral inguinal hernias who are identified during routine clinical practice in the participating trial centres (pre-screening). Suitable patients (see also inclusion and exclusion criteria) will be informed about the study by a medical member of the study group. After consent has been given, they are examined for the presence of all inclusion and absence of all exclusion criteria as part of the screening examination.

The treatment of patients then essentially corresponds to the routine laparoscopic repair (TAPP or TEP) of inguinal hernias (in accordance with IEHS guidelines), with the difference that one side is treated with a synthetic mesh material and the other side with biological mesh material. Which side is treated with which material is decided for each patient in advance by randomisation. After discharge, several follow-up examinations are carried out to record the study objectives (see Fig. 1). Discharge usually takes place 1-6 days after surgery. However, depending on the healing process, this can also occur later in individual cases and exceeding the 6 days therefore does not constitute a protocol violation. The reasons for the delayed healing process must be documented and the first follow-up is carried out as an inpatient in this case.

[figure not shown]

**Figure 1: Prodecure of the clinical trial**

At the last follow-up visit after two years, the patient can decide whether they would like to take part in further follow-up visits five and ten years after the operation. These further follow-up visits serve to collect additional long-term data and are analysed independently of the original study. If the patient does not consent, the study ends with the follow-up visit "24 months after surgery". After renewed consent, the patient remains in the study until a recurrence occurs on both sides, but for a maximum of ten years.

#### End of examination

The trial ends with the follow-up visit of the last study participant (LPLV) and the closing of the database.

## **4.2. Discussion of the study design**

The present study is a comparative study designed to show whether biological mesh material has advantages over synthetic mesh material for the repair of inguinal hernias. Both the surgical procedure and the mesh materials used correspond to the standard in clinical routine, the procedure is in accordance with the Guidelines for Laparoscopic (TAPP) and endoscopic (TEP) treatment of inguinal hernia of the IEHS and CE-certified commercial products are used. Only patients with bilateral inguinal hernias are included (approximately 20% of patients scheduled for surgery have bilateral hernias). This allows each patient to serve as a separate control. For this purpose, a decision is made by randomisation before the operation on which side the biological mesh material will be used and on the other side the synthetic mesh material will be used. This allows an ideal comparison between the two mesh materials without additional confounding variables.

### **4.3. Selection of the study population**

The study population is deliberately intended to represent as broad a range of patients as possible who suffer from bilateral inguinal hernias and come from routine clinical practice. Therefore, few restrictions are placed on the inclusion criteria. The exclusion criteria also represent a minimum that is either necessary for safety reasons or interferes with the endpoints.

A specific gender distribution is not required.

#### **4.3.1. Inclusion criteria**

- Age at least 18 years
- Written informed consent
- Unrestricted legal capacity
- Primary, bilateral inguinal hernias (if necessary, imaging confirmation by means of sonography/CT/MRI), if necessary, indication if one hernia is larger than the other
- Patient suitable for laparoscopic hernia surgery

#### **4.3.2. Exclusion criteria**

- Recurrent hernia
- Incarcerated hernia
- Acute systemic infection
- Expected non-compliance with any study requirement
- Severe comorbidity (ASA  $\geq$  4)
- Life expectancy < 12 months
- Chemotherapy within the last 4 weeks
- Radiotherapy within the last 2 months
- Known allergy to pig or bovine antigens
- Simultaneous participation in another study that interferes with this study
- Previous participation in this study

- Persons who are in a dependent/employment relationship with the sponsor or investigator
- Placement in an institution on the basis of a court or official order.

#### **4.4. Subsequent exclusion of study participants**

If one or more of the following reasons are present, study participants will be excluded from the clinical trial:

- At the request of the study participant (even without giving reasons)
- Based on the decision of an auditor (e.g. after a changed risk analysis)
- Based on the decision of the sponsor (e.g. following a changed risk analysis)
- In case of violation of inclusion or exclusion criteria
- Non-compliance of the study participant

The data collected up to the point of exclusion is used for analysis and the patient must agree to this in the declaration of consent.

A study participant is subsequently excluded from the clinical trial if the laparo-endoscopic treatment of the hernia with a biomesh is not performed (e.g. intraoperative complications, only one-sided hernia diagnosed intraoperatively, other surgical procedure performed, consent withdrawn shortly before the operation). As randomisation takes place up to 72 hours before the operation for organisational reasons, the patient is included in the clinical trial from this point in time. Without the surgical procedure or without the use of a biomesh, there is no data to be collected. Patients who are excluded from the trial after randomisation and before the start of the observation period are replaced by another trial participant in order to achieve the required number of cases. The randomisation sequence is continued, i.e. the following patient does not receive the randomised allocation of the patient who dropped out. The study will continue until the required number of analysable patients has been reached.

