#### *4.9.1.3. CRF: Operation data*

- Randomisation
- Patient treated as randomised?
- Date
- Duration of surgery (incision-suture)
- ASA classification
- Antibiotic prophylaxis yes/no?
- Adhesiolysis necessary yes /no
- Type of hernia (per side)
  - Medial/ lateral/ combined (classification according to Schumpelick)
  - Size (1=<1.5 cm, 2=1.5-3 cm, 3=>3 cm, classification according to Schumpelick)
- Drainage yes/no
- Fixation of the mesh yes/no, which adhesive
- Complications
  - Intestinal injury

- Bleeding incl. severity (mild/ moderate/ severe)
  - Injury to the bladder
  - Conversion
- Further interventions:
  - Removal of Meckel's diverticulum
  - Simultaneous umbilical hernia operation
  - other

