#### **6.1.1. Study populations**

The study is evaluated according to the intention-to-treat (ITT) principle, i.e. the right or left hernia is allocated to the group with biological mesh or synthetic mesh according to randomisation.

If mix-ups occur during the course of the study, i.e. the wrong sides were operated on (i.e. right/left instead of left/right), or both sides were operated on using the same procedure, then a protocol violation has occurred. In this case, a "Per-Protocol" (PP) analysis and an "As Treated" analysis are also carried out. In the per-protocol analysis, patients with protocol violations are excluded; in the as-treated analysis, the respective hernia is assigned to the material group (biological or synthetic).

Surgery-specific complications are also reported according to "As-Treated".

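### Section 4.4 excludes randomised patients when the biological mesh is not implanted, with no matching rule for the synthetic mesh, and so conflicts with the ITT rule in the synopsis and 6.1.1

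*Protocol*

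**What the plan says.** Section 4.4 places randomisation up to 72 hours before surgery and says that "the patient is included in the clinical trial from this point in time". It then sets the exclusion rule: "A study participant is subsequently excluded from the clinical trial if the laparo-endoscopic treatment of the hernia with a biomesh is not performed". Its examples are intraoperative complications, a hernia found to be one-sided, a different operation, and consent withdrawn shortly before surgery. The reason given is: "Without the surgical procedure or without the use of a biomesh, there is no data to be collected".

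On numbers, 4.4 says "Patients who are excluded from the trial after randomisation and before the start of the observation period are replaced by another trial participant" and "The study will continue until the required number of analysable patients has been reached". The start of the observation period is not defined. The same section also says that data gathered before the exclusion are used in the analysis.

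The synopsis says "All endpoints are analysed in the intention-to-treat population". Section 6.1.1 assigns each hernia to its randomised material. If sides are mixed up, or if "both sides were operated on using the same procedure, then a protocol violation has occurred", per-protocol and as-treated analyses are added to the ITT analysis. The operation form in 4.9.1.3 has an item "Patient treated as randomised", which presupposes that some patients who were not so treated remain in the data.

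**The concern.** Two rules cover the same patient and give different answers. The rule in 4.4 also depends on delivery of one arm's treatment only. Whether the biomesh is placed is decided after randomisation by the surgeon, whom 4.6.3 does not expect to be blinded.

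If 4.4 is followed, these patients have no 6-month pain score and no 2-year recurrence status. Section 6.1 leaves patients without any follow-up out of the recurrence analysis. A later analysis plan cannot recover visits that never took place. Recruiting to a target of analysable patients restores the count but not the randomised population. Recurrence is tested for non-inferiority against a margin of 3 percentage points, so a small selected group could matter.

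**Working it through.** **1. The rules side by side.** Sections 4.6.1 and 4.7.1.4 require the same technique (TAPP or TEP) on both sides. Treatment of both sides alike, as a violation in 6.1.1, must therefore mean the same mesh material.

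| Randomised patient, both hernias repaired | Section 4.4 | Section 6.1.1 |
|---|---|---|
| Synthetic mesh on both sides | Excluded, no data | In ITT; violation; PP and as-treated added |
| Biological mesh on both sides | No exclusion under this rule | In ITT; violation; PP and as-treated added |
| Biological and synthetic on swapped sides | No exclusion under this rule | In ITT; violation; PP and as-treated added |

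Only the first row conflicts, and it is the row in which the biomesh was not used.

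**2. The plan's own scale (6.1.5).** The half-width formula n = 1.96² × p(1−p)/w² with p = 0.05 gives 202.8 for w = 0.03 (plan: 203) and 456.2 for w = 0.02 (plan: 451, close). Then 451 × 1.10 = 496.1 (plan: 496). The contradiction does not depend on these figures. They only supply standard errors.

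**3. Standard errors of the difference in recurrence.**
- Implied by the plan's interval of ±2 points: 2/1.96 = 1.02 points.
- Independent sides at 5% and 8%, with 496 × 0.9 ≈ 446 pairs: √[(0.05 × 0.95 + 0.08 × 0.92)/446] = 1.65 points.

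**4. Effect of the exclusion (illustration).** Let q be the share excluded, D the excess recurrence in them on the side allocated to biomesh, and A the difference among those analysed. All differences are in percentage points. The difference over all randomised patients is

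(1−q) × A + q × D.

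Set it to +3, the margin. Then A = (3 − qD)/(1−q), and the shift is 3 − A. The chance of a false non-inferiority claim is Φ(−1.96 + shift/SE), which is 2.5% at zero shift. Both q and D are assumptions, because the protocol gives neither. A share of 2-5% of 496 is about 10-25 patients.

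| q | D | A | Shift | SE 1.65 | SE 1.02 |
|---|---|---|---|---|---|
| 2% | 10 | (3 − 0.2)/0.98 = 2.86 | +0.14 | 3.1% | 3.4% |
| 5% | 20 | (3 − 1.0)/0.95 = 2.11 | +0.89 | 7.8% | 13.9% |
| 2% | 0 | 3/0.98 = 3.06 | −0.06 | 2.3% | 2.2% |
| 5% | 0 | 3/0.95 = 3.16 | −0.16 | 2.0% | 1.7% |

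The sign changes at D = 3. Above that, exclusion favours the biological mesh; below it, exclusion works against it. No comparable figure is offered for pain, because the protocol gives nothing on pain in such patients.

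**The case against.** The strongest reply is that 4.4 deals with the study operation not taking place, whereas 6.1.1 deals with mix-ups. Two of the four examples, withdrawn consent and a one-sided hernia, have nothing to do with the mesh. Every patient is allocated one biomesh, so its mention may be loose wording for the study procedure. Both sides share one technique, so a conversion prompted by either side would also end laparo-endoscopic biomesh treatment. Whole patients are dropped, so the arms stay equal in size. This stands in part: the mesh-independent reasons can justify a modified ITT set, and the conflict is confined to patients who were repaired without a biomesh. It does not remove that conflict, because 4.4 names non-use of a biomesh as sufficient by itself for collecting nothing.

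A reader might infer more than the text supports:
- **That bad outcomes of the biomesh are dropped.** They are not. Recurrence or pain after an implanted biomesh stays in the analysis.
- **That the bias runs towards non-inferiority.** This needs D above 3 points. A patient with synthetic mesh on both sides may have D near zero, and the shift then goes slightly the other way.
- **That serious intraoperative complications vanish from the safety count.** Section 4.4 keeps data obtained before exclusion, 4.9.1.3 records these events on the operation form, and 6.1.1 reports surgery-specific complications as treated. The no-data sentence makes this unclear; it does not state a removal.
- **That every excluded patient is replaced.** Replacement is limited to exclusions before an undefined start of observation.

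**Conclusion.** The point holds as a contradiction with consequences for both primary endpoints. Sections 4.4 and 6.1.1 cannot both be followed for a randomised patient repaired with synthetic mesh on both sides, and the exclusion is tied to one arm's material only. As 4.4 is written, the analysed set is selected on successful biomesh implantation.

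The size and direction of any bias are unknown. Under the assumed 2-5% excluded, false non-inferiority at a true +3 points lies between 3.1% and 13.9% with a 10-20 point excess, and between 1.7% and 2.3% with none, against 2.5% nominal. The upper end requires 5% excluded, a 20-point excess and the smaller standard error together. Correction should not wait for evidence on direction, because outcomes that were never collected cannot be restored at analysis.

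**What to change.** Reconcile 4.4 with 6.1.1 as follows:
- Limit exclusion and replacement to reasons that do not depend on which mesh was placed, such as consent withdrawn before surgery, operation not done, or a one-sided hernia. Define when the observation period starts.
- Follow every randomised patient with both hernias repaired, and analyse each side in ITT as allocated.
- Remove the part of the no-data sentence that refers to not using a biomesh.
- State that intraoperative complications already recorded are reported for all operated patients, in line with the existing rule on data obtained before exclusion.

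The cost is one rewritten paragraph, the usual follow-up visits for a few more patients, and an estimate that may be less favourable to the biological mesh.
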